## 222     **6.1 Recruitment and Baseline Assessment**

223     Subjects who meet the conditions of 4.1 of this research protocol will undergo a series of functional  
224     examinations as necessary research indicators for clinical research. The physicians at the outpatient  
225     clinic who recruited patients did not participate in the randomization and treatment. The main  
226     examination items include but are not limited to the following examination items:

- 227     (1) Physical examination (weight, height, body surface area)
- 228     (2) Vital signs check: temperature, pulse, heart function check
- 229     (3) Routine blood tests: hemoglobin, white blood cells, platelets, etc.
- 230     (4) Liver and kidney function tests
- 231     (5) bone marrow imaging, bone marrow biopsy
- 232     (6) Leukemia residual disease (MRD), related gene mutation detection

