265     After hematopoietic reconstruction to 1 year after transplantation, clinicians were blinded to the  
266     treatment allocation will access:

267     (1) Routine blood tests, liver and kidney function tests, CMV and EBV and other viral indicators (at  
268     least monthly)

269     (2) Bone marrow imaging, bone marrow biopsy (monthly)

270     (3) MRD, related gene mutation detection (monthly)7. Safety and Adverse Events

271     Safety will be measured and assessed daily by documenting potential adverse effects of treatment.  
272     Patients will be tested for potential toxicity that may arise from the treatment through tests such as  
273     medical history, physical examination, blood tests, etc.

274     **6.7 Recording of Adverse Events**

275     Investigators can gather information on adverse events through special questions or, in certain  
276     circumstances, tests in their interactions with each patient. All information about adverse events needs  
277     to be entered into the database immediately and into the Adverse Events module of the Case Report  
278     Form (CRF). All apparently relevant signs, symptoms, and abnormal diagnoses need to be entered into  
279     the database and grouped under the same diagnosis.

280     All adverse events that occurred during the study period were required to be recorded. All adverse  
281     events needed to be followed until resolved, stabilized, or until confirmed that study treatment or

282 participation was not an issue. Serious adverse events that persisted at the end of the study had to be  
283 followed until final results were determined. Any serious adverse events that occur after the study and  
284 that may be related to study treatment or study participation need to be recorded and reported promptly.  
285 If any subject has the following conditions within 2 weeks of receiving cell reinfusion therapy , the  
286 study will be required to be re-reviewed, and the clinical trial at this stage will be suspended:

- 287 (1) Respiratory failure requires artificial respirator.  
288 (2) Grade 4 (life-threatening) toxicity due to treatment regimen.  
289 (3) Death.

290

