## 291 **7. Randomization**

292 A permuted block randomization method was used in this study. At each research center, consenting  
293 eligible participants were randomly assigned in a 1:1 ratio to the MSC group and control group using a  
294 computer-generated permuted block randomization schedule by statisticians who were not involved in  
295 the recruitment, treatment and therapeutic effect evaluation.. The permuted block size was randomly  
296 generated from among the numbers 4 and 6.

297 With permuted block of size four there are six possible patterns: AABB, ABAB, ABBA, BAAB,  
298 BABA, and BBAA.

299 With permuted block of size six there are 20 possible patterns:

AAABBB ABABAB BAAABB BABBAA

AABABB ABABBA BAABAB BBAAAB

AABBAB ABBAAB BAABBA BBAABA

AABBBA ABBABA BABAAB BBABAA

ABAABB ABBBAA BABABA BBBAAA

300

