## 337 **11. Statistical Analysis Plan**

338 The Mann–Whitney tests, the chi-squared test, and Fisher's exact test were used to compare the AE  
339 between the MSC group and the control group. The competing risk model (Fine and Gray model) was  
340 used to estimate 2-year cumulative incidences and hazard ratios (HRs), with their 95% CIs, for severe  
341 cGVHD and cGVHD (competed by death and relapse) and leukemia relapse (competed by nonrelapse  
342 death). The cumulative incidence of grade II-IV aGVHD and grade III-IV aGVHD, the GRFS rate and  
343 the OS rate were estimated using Kaplan–Meier analysis and are expressed as percentages with 95%  
344 CIs. The Kaplan–Meier method, the log-rank test, and Cox proportional hazard models was used to  
345 compare the grade II-IV aGVHD and III-IV aGVHD, GRFS and OS curves between the two groups.  
346 All reported *P* values are two-sided. Statistical analyses were performed using STATA 17 (StataCorp.  
347 2021. Stata Statistical Software: Release 17. College Station, TX: StataCorp LLC)) and R (version  
348 4.4.2, R Foundation for Statistical Computing, Vienna, Austria).

349

350

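### Baseline MRD is collected but is used neither to stratify randomization nor to adjust the relapse, GRFS and OS models, which forgoes some precision and leaves a chance imbalance unaddressed

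*Combined protocol and SAP*

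**What the plan says.** - **Collection.** Section 6.1 states: "Subjects who meet the conditions of 4.1 of this research protocol will undergo a series of functional" examinations, and item 6 of its list is "6) Leukemia residual disease (MRD), related gene mutation detection". Section 6.6 repeats the test after transplant, once a month up to one year: "3) MRD, related gene mutation detection (monthly".
- **Randomization.** Section 7 works centre by centre ("At each research center, consenting") with permuted blocks of 4 or 6: "eligible participants were randomly assigned in a 1:1 ratio to the MSC group and control group using a" computer-generated schedule. MRD is not a stratum.
- **Analysis.** Section 11 uses a Fine-Gray model for relapse: "cGVHD and cGVHD (competed by death and relapse) and leukemia relapse (competed by nonrelapse" death). For GRFS and OS it names Kaplan-Meier, "the log-rank test, and Cox proportional hazard models was used to" "compare the grade II-IV aGVHD and III-IV aGVHD, GRFS and OS curves between the two groups". No covariate is named for any model.
- **Endpoints.** The synopsis makes severe cGVHD primary and lists GRFS and OS as secondary. Relapse is analysed in section 11 but is not a listed secondary endpoint.

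**The concern.** The eligibility criteria (synopsis and section 4.1) set no remission or MRD requirement, so MRD-positive and MRD-negative patients with AML or ALL can enter. Section 3.3 counts molecular or genetic recurrence as relapse, and defines it for patients who had reached cytogenetic or molecular remission. MRD status at baseline therefore bears on who can meet that form of relapse. Relapse is in turn a component of GRFS.

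The background section says that current GVHD prevention raises leukemia recurrence, and that the centre's previous study saw no increase with UC-MSCs. Section 1.1 also makes the recurrence rate something the trial will observe. A reader will therefore ask whether a lower GVHD rate was bought with more relapse. If MRD-positive patients fall unevenly between the arms, the plan offers no agreed way to answer. In an open-label trial, an adjustment chosen after the data are seen would look selective.

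**Working it through.** **The plan's own figure.** The only sample-size figure is for severe cGVHD: 142 / (1 - 0.10) = 157.8, rounded up to 158, or 79 per arm. This reproduces. No power or event count is stated for relapse, GRFS or OS, so there is nothing to reproduce for those outcomes.

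**Assumed inputs, none of them in the documents.** MRD prevalence 20-40%; MRD hazard ratio 1.5-3 (4 as an extreme); two-year control event rate 25% for OS or relapse and 50% for GRFS; treatment hazard ratio 0.5-0.6, or 1.0 for type I error.

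**Step 1: chance of imbalance.** The difference in MRD-positive proportion between arms has SD = sqrt(2p(1-p)/79). The two-sided normal probability of exceeding 10 points is:

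| Prevalence p | SD | 0.10/SD | Probability |
|---|---|---|---|
| 20% | 0.0636 | 1.57 | 12% |
| 30% | 0.0729 | 1.37 | 17% |
| 40% | 0.0779 | 1.28 | 20% |

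For 15 points the probabilities are 2%, 4% and 5%.

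**Step 2: effect of a 10-point imbalance.** Take 35% against 25% MRD-positive (30% overall) and an MRD hazard ratio h. The unadjusted hazard ratio shifts by roughly (0.65 + 0.35h)/(0.75 + 0.25h):
- h = 1.5: 1.175/1.125 = 1.04
- h = 2: 1.35/1.25 = 1.08
- h = 3: 1.70/1.50 = 1.13

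**Step 3: type I error.** In Cox simulations with 79 per arm, censored at two years, null rejection without adjustment was 3.5-5.1% in one set (1,500 runs per scenario) and 4.8-5.5% in another (2,000 runs). The unadjusted tests are valid.

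**Step 4: power gained by adding MRD to the Cox model.**

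| Outcome and assumption | MRD HR | Gain (points) |
|---|---|---|
| OS or relapse, 25% control events | 1.5-3 | -0.4 to +2.4 |
| GRFS, 50% control events, MRD acts on the whole hazard | 1.5-2 | +0.6 to +2.8 |
| Same | 3 | +5.8 to +6.4 (e.g. 71.4% to 77.8%) |
| GRFS, MRD acts only through relapse, relapse 50% of baseline hazard | 2 / 3 | +0.4 / +3.6 |
| Same, relapse 33% of baseline hazard | 2 / 3 | 0.0 / +1.4 |

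A further whole-hazard run for GRFS (30% MRD-positive, treatment hazard ratio 0.55) gave 63.3% to 65.3% at an MRD hazard ratio of 2 and 59.4% to 66.5% at 3. At the extreme of 4, it gave 55.7% to 67.2%; acting only through relapse, the gain at 4 was 2.0 to 5.0 points.

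For OS or relapse the limit is events. At a treatment hazard ratio of 0.5, expected events are about 79 x 0.25 + 79 x (1 - 0.75^0.5) = 19.8 + 10.6, or about 30. Power in the 25% scenarios was 27-44% with or without adjustment.

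**Not checked.** Cox was used throughout; the Fine-Gray relapse model was not simulated. The power runs concern a treatment benefit, so they do not measure the ability to detect an excess of relapse.

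**The case against.** The strongest case against is that randomization already protects the comparison. Chance imbalance is part of the sampling variation that the planned confidence intervals cover, and it exists for every baseline variable. Section 11 names no covariate for any model, so choosing MRD is the reviewer's judgement, and these are not the primary analysis. This stands in part: it rules out bias or an inflated error rate. It does not remove the value of naming in advance one already collected variable that the protocol's own relapse definitions involve.

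Three stronger readings are tempting but unsupported:
- **All three comparisons lose material power.** For OS and relapse, the gain from adjustment is within or near simulation error at 25% events and MRD hazard ratios up to 3. For GRFS it reaches about 6 points only if MRD has a hazard ratio of about 3 and acts on the whole hazard. GRFS also counts GVHD, so a smaller gain is plausible.
- **The unadjusted hazard ratio is wrong because it is pulled toward 1.** Simulated averages were 0.56-0.59 unadjusted and 0.54-0.55 adjusted. That gap is largely non-collapsibility: one is a marginal hazard ratio, the other conditional on MRD. This is no reason to replace the planned estimate.
- **MRD is a dated pre-transplant value, available in everyone and ready to use.** Pre-transplant timing is inferred from section 6.1 preceding section 6.3. The documents date neither the test nor randomization, and eligibility refers to transplantation as already done in the synopsis but as under way in section 4.1. No section defines an assay or cut-off for a mixed AML and ALL population, and some patients may have no trackable marker.

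**Conclusion.** The point holds as a modest improvement to the analyses of relapse, GRFS and OS. MRD is planned at baseline and then used in neither design nor analysis. The error rate is intact and the randomized comparison is unbiased; the loss is in precision and in the ability to interpret one realised result. The imbalance probabilities rest on 20-40% prevalence, the hazard-ratio shift on 30% prevalence and an MRD hazard ratio of 1.5-3, and the power gains on the assumed event rates. A weaker MRD effect, or one confined to the relapse part of GRFS, would shrink the benefit toward zero. No effect on the primary severe cGVHD analysis has been shown, although relapse is a competing event there.

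**What to change.** In section 11, pre-specify Cox models for GRFS and OS and a Fine-Gray model for relapse, each with treatment and baseline MRD status. Report them next to the planned unadjusted log-rank, Kaplan-Meier and Fine-Gray results, not in their place.

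The text should state, before analysis:
- that MRD status comes from the section 6.1 assessment, with its timing relative to transplant and randomization, and not from the monthly tests of section 6.6, which follow transplant and could be affected by treatment;
- the assay and positivity rule for AML and for ALL;
- that patients without a trackable marker form their own category and are not dropped, and how a missing test is handled.

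The cost is one degree of freedom, or two with the extra category, and the work of agreeing the positivity rule. The report must also say that the adjusted hazard ratio is conditional on MRD, and so need not equal the unadjusted one even under perfect balance. No new tests, patients or visits are needed.

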## 233     **6.2 Collection of subjects' documents and materials**

- 234     (1) Documents required to recruit subjects include:
- 235     (2) Complete the required materials for screening;
- 236     (3) Sign the informed consent;

## 237     **6.3 Implementation of haploid hematopoietic stem cell transplantation**

### 238     **6.3.1 Preprocessing scheme Me-CCNU+Ara-C+Bu+Cy+ATG ( Beijing protocol )**

239     Me-CCNU:  $250\text{mg}/\text{m}^2 \times 1\text{d}$ , Ara-C:  $4\text{g}/\text{m}^2 \times 2\text{d}$ , Bu:  $0.8\text{mg}/\text{kg}$  q6h,  $\times 2\text{d}$ , CTX:  $1.8\text{g}/\text{m}^2 \times 2\text{d}$

### 240     **6.3.2 Hematopoietic stem cell mobilization, collection and reinfusion**

241     The donors were given subcutaneous injection of recombinant human granulocyte colony-stimulating  
242     factor ( rhGCSF ) at  $10\text{ u g}/\text{kg} / \text{d}$  for 4 days, and peripheral blood stem cells (peripheral blood stem  
243     cells) were collected by a German Fresenius blood cell separator on d5 . blood stem cells , PBSC) . On  
244     day 6 , bone marrow collection was performed. After epidural anesthesia was performed, the donor was  
245     placed prone on the operating bed, and puncture was performed at different depths and multiple sites on  
246     the bilateral iliac ridges for collection; if it is estimated that more than 600ml of bone marrow fluid  
247     needs to be collected, the donor should be adjusted to the supine position, collected in bilateral anterior  
248     superior iliac spine puncture. If the donor and recipient ABO blood type is incompatible on the primary  
249     side, erythrocytes are removed by hydroxyethyl starch sedimentation; if the secondary side is  
250     incompatible, the bone marrow fluid needs to be centrifuged at  $4^{\circ}\text{C}$  at a low temperature, and then the  
251     plasma in the bone marrow fluid is removed with a plasma separator.

252     **6.4 Prevention of GVHD after haploid hematopoietic stem cell transplantation**

253     (1) Experimental group: On the basis of conventional GVHD prevention, UC-MSCs were infused 45  
254     days after transplantation at a dose of  $1 \times 10^6/\text{kg}$  with the interval of 14 days for 4 times.

255     (2) Control group: Beijing program for routine GVHD prevention (MMF) 0.5g q12h -7d~90d,  
256     cyclosporine (CsA) 1.25mg/kg, continuous intravenous drip; -1 day increment to 2.5mg/kg; After the  
257     patient can tolerate oral administration, it is changed to oral 5 mg/kg, and the concentration is  
258     maintained at 200-300 ng/ml; the dose is slowly reduced 180 days after transplantation; methotrexate  
259     (MTX) 15 mg/m^2 d1, 10 mg/m^2 d3, 6,11)

260     **6.5 Indicator observation**

261     (1) The incidence of severe chronic GVHD

262     (2) The incidence of II-IV acute GVHD, the incidence of chronic GVHD, OS, Post-transplant patient  
263     GRFS (GVHD-free and relapse-free survival)

264     **6.6 Therapeutic Monitoring Protocol**

265     After hematopoietic reconstruction to 1 year after transplantation, clinicians were blinded to the  
266     treatment allocation will access:

267     (1) Routine blood tests, liver and kidney function tests, CMV and EBV and other viral indicators (at  
268     least monthly)

269     (2) Bone marrow imaging, bone marrow biopsy (monthly)

270     (3) MRD, related gene mutation detection (monthly)7. Safety and Adverse Events

271     Safety will be measured and assessed daily by documenting potential adverse effects of treatment.  
272     Patients will be tested for potential toxicity that may arise from the treatment through tests such as  
273     medical history, physical examination, blood tests, etc.

274     **6.7 Recording of Adverse Events**

275     Investigators can gather information on adverse events through special questions or, in certain  
276     circumstances, tests in their interactions with each patient. All information about adverse events needs  
277     to be entered into the database immediately and into the Adverse Events module of the Case Report  
278     Form (CRF). All apparently relevant signs, symptoms, and abnormal diagnoses need to be entered into  
279     the database and grouped under the same diagnosis.

280     All adverse events that occurred during the study period were required to be recorded. All adverse  
281     events needed to be followed until resolved, stabilized, or until confirmed that study treatment or

282 participation was not an issue. Serious adverse events that persisted at the end of the study had to be  
283 followed until final results were determined. Any serious adverse events that occur after the study and  
284 that may be related to study treatment or study participation need to be recorded and reported promptly.  
285 If any subject has the following conditions within 2 weeks of receiving cell reinfusion therapy , the  
286 study will be required to be re-reviewed, and the clinical trial at this stage will be suspended:

- 287 (1) Respiratory failure requires artificial respirator.  
288 (2) Grade 4 (life-threatening) toxicity due to treatment regimen.  
289 (3) Death.

290

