| Observation period       | (1) Real-time observation of the occurrence of acute and chronic GVHD after transplantation;
(2) Follow-up: relapse, death and HSCT related complication                                                                                                                                                                                                                                                                                                                                                                                                                                                                                              |
| Primary Endpoint         | Severe chronic GVHD                                                                                                                                                                                                                                                                                                                                                                                                                                                                                                                                                                                                                                      |
| Secondary Endpoint       | Chronic GVHD, acute GVHD, Overall survival (OS), GVHD-free and Relapse-free survival (GRFS).                                                                                                                                                                                                                                                                                                                                                                                                                                                                                                                                                             |

|                   |                                                                                            |
|-------------------|--------------------------------------------------------------------------------------------|
| Safety evaluation | Incidence of adverse events (AE) and severe AE during 45 days to 100 days after haplo-HSCT |
| Study period      | 2016.4-2022.2                                                                              |

29

30

31

32  
33  
34  
35  
36  
37  

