## 148 **3. Clinical trial design**

### 149 **3.1 Overall Design**

150 A multicenter, randomized, controlled, open clinical trial was designed to explore the efficacy and  
 151 safety of umbilical cord-derived MSCs in preventing graft-versus-host disease after haploid  
 152 hematopoietic stem cell transplantation.

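### Section 6.7 lets adverse event follow-up end on a causality judgement, which in this open trial may be reached sooner for control patients and leave their non-serious events less completely graded

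*Combined protocol and SAP*

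**What the plan says.** Section 6.7 (Recording of Adverse Events) starts from a complete recording rule: "All adverse events that occurred during the study period were required to be recorded". It then sets the end of follow-up: all adverse "events needed to be followed until resolved, stabilized, or until confirmed that study treatment or" participation can be ruled out. There are therefore three exits: resolution, stabilisation, and a confirmed finding that neither study treatment nor participation was responsible. No arm is named.

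Two further rules concern serious events. Those still present when the study ends are not released by causality; the text runs "participation was not an issue. Serious adverse events that persisted at the end of the study had to be" "followed until final results were determined". Those that arise after the study are covered only if they are events "that may be related to study treatment or study participation need to be recorded and reported promptly".

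The synopsis gives the safety evaluation as "Incidence of adverse events (AE) and severe AE during 45 days to 100 days after haplo-HSCT". Section 3.4 grades events on five levels, with reference to CTCAE v4.0. Section 11 says: "The Mann–Whitney tests, the chi-squared test, and Fisher's exact test were used to compare the AE" between the two groups. It does not say whether incidence, grade, count, duration or outcome is tested. Section 3.1 describes the design: "A multicenter, randomized, controlled, open clinical trial was designed".

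**The concern.** In a randomised comparison of harms, the rule that decides how long an event is watched should not depend on which treatment the patient received or on what the investigator believes about cause. The third exit depends on both. When investigators know the allocation, it is easier to rule out UC-MSC for a patient who never had it than for one who had an infusion the week before. If control events are closed earlier, a later worsening may not reach the graded record, and the MSC arm would look worse on severity without being so. If investigators instead readily put MSC-arm events down to the transplant, the distortion runs the other way.

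Safety is part of the stated purpose in section 2, and the adverse event comparison is the only item that the synopsis labels as safety evaluation. Its severity component should rest on equal ascertainment in the two arms.

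**Working it through.** The plan has no figure to reproduce here. The check sets the rules side by side and asks which statistic could be affected.

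**1. Does exposure differ in a way that matters to the third exit?** Sections 5.1 and 6.4 give the MSC arm routine prophylaxis plus four infusions, and the control arm routine prophylaxis alone. The term study treatment is not defined. If it means UC-MSC only, controls have none. If it includes the prophylaxis, both arms have that and the MSC arm has the infusions as well. On either reading the MSC arm has at least as many candidate causes to exclude, so on exposure grounds the exit is never easier to meet there. The suspension rule in the same section is built around cell reinfusion, which suggests that the cells are what the section has in mind.

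**2. Does this overlap with the safety window?** The first infusion is at day 45 and the interval is 14 days (section 6.4): 45 + 14 × (0, 1, 2, 3) = days 45, 59, 73 and 87. The window ends at day 100, which is 100 − 87 = 13 days after the last infusion. With infusions on schedule, an MSC patient is therefore never more than 14 days from the latest infusion anywhere in the window. That is the period in which excluding UC-MSC as a cause is hardest.

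**3. Who makes the judgement?** Section 6.6 describes the clinicians who do scheduled monitoring to 1 year as blinded. Section 6.7 gives the collection of adverse events to investigators and does not call them blinded. Someone who does not know whether a patient received UC-MSC could hardly confirm that it was not the cause.

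**4. Which results depend on how long an event is followed?**

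| Result | Can early closure change it? |
|---|---|
| Incidence of any adverse event, day 45–100 | No. The event counts once recorded. |
| Incidence of severe adverse events, day 45–100 | Yes, if severe is judged by grade and the event worsens inside the window after closure. |
| Comparison of grade (Mann–Whitney would suit it) | Yes, if grade is what is tested. Section 11 does not say. |
| Serious events persisting at study end | Not through this exit. They are followed to a final result in both arms. |
| Serious events arising after the study | Outside the day 45–100 comparison. |

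Section 6.7 also groups related signs and symptoms under one diagnosis, so a worsening need not create a new record.

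**5. Can the effect be sized?** For arm a, let p be the proportion of patients with a non-severe event in the window, c the share of these closed by the third exit, w the chance of worsening to severe inside the window after closure, and r the chance that the worsening is recorded anyway. The proportion of patients whose severe event is missed is

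L(a) = p × c × w × (1 − r).

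The observed difference (MSC minus control) equals the true difference plus L(control) − L(MSC). The documents give none of p, c, w or r for either arm. If r = 1 the bias is zero. If c is higher in controls and the other terms are equal with r below 1, the bias works against UC-MSC. If c is higher in the MSC arm, it works in favour of UC-MSC. Neither size nor sign follows from the text.

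**The case against.** The strongest reply is that the rule is worded identically for both arms and that other provisions limit the damage. Much of this stands.

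- A reader might infer that the third exit is met automatically for every control patient. The text does not support that. It asks for confirmation, it covers participation as well as treatment, and control patients also participate. The control regimen appears under section 5 (Treatment options) and could itself count as study treatment.
- A reader might infer that an MSC patient's event has to be followed to resolution. It does not: all three exits, including stabilisation and the causality exit, are open in both arms.
- A reader might infer that late serious events are collected from one arm only. The post-study rule also covers events related to participation, and such events lie outside the comparison window in any case.
- Section 6.6 schedules blood, liver, kidney and viral tests at least monthly to 1 year without distinction by arm, and safety is to be assessed daily. Section 6.7 requires all events in the study period to be recorded and all information about them to be entered at once. Many laboratory worsenings would be detected whatever the status of the adverse event entry.
- The safety comparison is not the only harm information. Section 11 also analyses relapse, with nonrelapse death competing, and compares overall survival.

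These points narrow the concern but do not remove it. Detecting a worse value on a scheduled test is not the same as reopening a closed event and regrading it, and nothing in section 6.7 requires that. The rule on persisting serious events does not help a non-serious event that was closed before it worsened.

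**Conclusion.** The concern holds in a limited form. Section 6.7 contains a causality-based end to follow-up that can be met sooner for control patients in an open trial. Non-serious events that worsen after early closure may therefore be graded less completely in that arm. The exposed results are the severe adverse event count for day 45–100 and any graded comparison under section 11; the incidence of any adverse event is untouched.

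This rests on three assumptions: that severe is judged at least partly by grade, that investigators who know the allocation apply the third exit, and that a later worsening is not always added to the record. It would be too strong to say that the arms were in fact followed for different lengths, or that the safety comparison loses its basis in randomisation. The documents show that the rule permits unequal follow-up, not that it occurred, and they provide no rates from which to build an estimate. The change is worth making because it is cheap, not because a large bias has been shown.

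**What to change.** In section 6.7:

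1. Delete the exit that depends on study treatment or participation being ruled out.
2. Require every adverse event in both arms to be followed to resolution, stabilisation, death or end of study follow-up, whatever its cause.
3. Require the recorded grade to be updated to the worst grade reached within day 45–100, so that a worsening within one diagnosis is captured.
4. Record causality as a separate field that does not end follow-up.

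The cost is a short protocol change and more follow-up entries for control events, in patients who are already seen at least monthly to 1 year. If data collection has ended, as the study period in the synopsis (2016.4–2022.2) suggests, the sponsor can instead tabulate the reason for and day of adverse event closure by arm, check later scheduled laboratory results within the window for events closed as unrelated, and state any remaining limitation next to the severe adverse event comparison.
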